### Non-invasive ischaemia testing in ANOCA

The available non-invasive ischaemia tests were all validated for the detection of obstructive epicardial CAD. There has been a low yield of inducible myocardial ischaemia in ANOCA patients with traditional non-invasive ischaemia tests (e.g. exercise ECG testing, myocardial perfusion scintigraphy and stress echocardiography).^23^ However, non-invasive methods (namely stress perfusion positron emission tomography (PET) and CMR which image earlier in the ischaemic cascade and have greater spatial resolution) may provide new insights into the burden of myocardial ischaemia in patients with ANOCA. PET is the most studied modality for the assessment of myocardial perfusion and is considered to provide the reference standard assessment of MBF, but in real-world clinical practice, availability is limited due to cost. Conversely, CMR is more widely available and use is increasing.^24 25^

Coronary microvascular disease may be revealed by a deficit in MBF during stress CMR. The spatial distribution of this abnormality typically involves the subendocardium, which is the location of the microvascular plexus.^26^ In contrast, vasospastic angina occurs due to spontaneous spasm of the epicardial and microvascular vasculature. Vasospastic angina may not be detected by conventional stress testing that routinely use adenosine (an endothelial-independent vasodilator). The available data are conflicting on the role of perfusion CMR in patients with ANOCA.^26–28^ In contrast to qualitative analysis, semiquantitative perfusion methods have been investigated, and reduced myocardial perfusion reserve index (MPRi) has been found in patients with ANOCA.^29^ The incremental diagnostic value of fully quantitative perfusion CMR in patients with ANOCA is unknown.

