### The Stratified Medical Therapy Using Invasive Coronary Function Testing In Angina (CorMicA) trial

The Stratified Medical Therapy Using Invasive Coronary Function Testing In Angina (CorMicA) clinical trial is a proof-of-concept, prospective, blinded, randomised, sham-controlled study comparing two management approaches to the clinical problem of patients with ANOCA.^32^ CorMicA tests the hypothesis that stratified medicine guided by invasive coronary artery function testing (interventional diagnostic procedure (IDP)) in patients with ANOCA will facilitate diagnosis of the underlying disease endotype, direct therapeutic interventions aligned to the endotype and result in improved angina and well-being.^32^ Patients undergoing elective invasive coronary angiography for investigation of angina at two UK centres will be screened. Eligible patients with ANOCA (n=150) will be immediately randomised 1:1 to either coronary vascular function-guided diagnosis and treatment (intervention group/IDP disclosed) or not (control group/IDP sham procedure, results not disclosed) (figure 1).

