Patients in the control group will receive standard care based on the interpretation of the invasive coronary angiogram alone. Patients in the intervention group will have care based on the disease endotypes disclosed by invasive tests of artery function, and pharmacotherapy linked to the underlying disease endotype will be commenced.^32^ In each case, the diagnosis (endotype) will be assessed by the attending cardiologist before and after the coronary angiogram. In the intervention group, the diagnosis is re-evaluated after disclosure of the coronary function test results at the end of the invasive procedure. The primary outcome is the mean difference in the within-subject change in Seattle Angina Questionnaire score between the groups at 6 months from baseline. A prespecified substudy of the CorMicA trial investigated the frequency of peripheral microvascular dysfunction in patients with ANOCA.^33^

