### Hypothesis

We hypothesise that abnormal myocardial perfusion, as revealed by a novel fully quantitative pixel-wise CMR perfusion sequence, will be prevalent in a contemporary UK cohort of patients presenting with ANOCA and that multiparametric CMR imaging will be clinically useful in the diagnostic pathway of patients with ANOCA.

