### Aims

We aim to assess the diagnostic validity of quantitative stress perfusion CMR in patients with ANOCA and specific disease endotypes of coronary vascular dysfunction. Our specific aims are to assess:

The proportion of ANOCA patients with abnormal myocardial perfusion. There is no accepted threshold for abnormal MPR. Thresholds for reduced CFR of 1.5–2.6 have been described, however <2.0 is commonly used.^10 34–38^ We will therefore assess the concordance of patient classification using this MPR <2.0 threshold against endotypes determined by invasive testing. Second, we will assess the MPR value with the highest area under the curve (AUC) for classification of microvascular angina based on the invasive tests (reference classification). Third, we will assess the proportion of ANOCA endotypes with other abnormal perfusion metrics (reduced stress MBF, abnormal endocardial:epicardial MBF ratio and abnormal myocardial dyssynchrony index).^39^
The diagnostic accuracy of the perfusion CMR metrics for abnormal invasive tests of coronary artery function (IMR >25, CFR <2.0 and RRR <2.0) and the associations between specific disease endotypes and myocardial perfusion in patients with ANOCA. We also aim to assess the correlation between abnormal CMR-derived perfusion and invasive tests of coronary artery function, of qualitative versus quantitative perfusion methods.The proportion of patients with ANOCA and abnormal myocardial tissue characterisation derived from CMR (as revealed by T1 parametric mapping and late gadolinium enhancement (LGE) imaging) and its association with abnormal myocardial perfusion.The associations between baseline patient characteristics and abnormal myocardial perfusion.The proportion of patients with a change in diagnosis based on quantitative CMR findings, as compared with the initial diagnosis by the attending cardiologist based on the coronary angiogram.

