### Participants

Consecutive outpatients undergoing clinically indicated elective diagnostic angiography for investigation of suspected angina will be screened and invited to participate in the CorMicA trial. Informed consent is obtained before the invasive coronary angiogram. A minimum of 400 consecutive patients undergoing elective invasive coronary angiography is expected to be screened to enrol 150 subjects with ANOCA within 24 months. Consenting patients who are not randomised (e.g. demonstrated to have obstructive epicardial disease or logistical reasons) will enter a registry. Only patients randomised in the CorMicA trial (both in the intervention and control groups) are eligible to participate in the CorCMR substudy.

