## Discussion

The British Heart Foundation CorMicA trial will assess a routine stratified medicine strategy in a large cohort of prospectively enrolled patients with ANOCA. The prespecified CorCMR substudy will involve comprehensive invasive tests of coronary artery function paired with multiparametric perfusion CMR studies. The analysis will provide information on the diagnostic value of quantitative pixel-wise mapping of myocardial perfusion in this population.

Contemporary guidelines recommend functional testing, including with CMR, to assess for myocardial ischaemia in patients in whom multidetector CT coronary angiography has shown CAD of uncertain functional significance or is non-diagnostic.^49^ Increasingly, patients are referred to the catheter laboratory based on the results of anatomical imaging using CT coronary angiography or with no prior tests based on symptoms and a high likelihood of CAD.^49 50^ The CorCMR substudy in CorMicA aims to inform this gap.

The CorCMR substudy will be performed on a 1.5 Tesla MRI scanner. In comparison, 3.0 Tesla imaging permits improved signal-to-noise ratio and provides higher in-plane spatial resolution perfusion imaging.^51 52^ However, CMR imaging in the NHS is most widely performed at 1.5 Tesla, hence the results from CorCMR are clinically relevant and transferable.

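### The change-in-diagnosis aim counts changes towards and away from the invasive endotype alike, so on its own it cannot support the hypothesis of clinical usefulness

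*Protocol article*

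**What the plan says.** The Aims section of the protocol article ends with "The proportion of patients with a change in diagnosis based on quantitative CMR findings". The clause that names the comparator reads "as compared with the initial diagnosis by the attending cardiologist based on the coronary angiogram". Both the statistic (proportion changed) and the comparator (the angiogram-based diagnosis) are therefore fixed in the text. The Hypothesis section says that "multiparametric CMR imaging will be clinically useful in the diagnostic pathway of patients with ANOCA".

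The article also plans what is needed to score each change:

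- **Starting diagnosis.** In the introductory description of the CorMicA trial, after Table 1, "the diagnosis (endotype) will be assessed by the attending cardiologist before and after the coronary angiogram", and this applies to every case.
- **Invasive reference in both arms.** The control arm is described as "control group/IDP sham procedure, results not disclosed", so testing is done there too. Participants states: "Only patients randomised in the CorMicA trial (both in the intervention and control groups) are eligible to participate in the CorCMR substudy".
- **Pairing and blinding.** The Discussion describes "comprehensive invasive tests of coronary artery function paired with multiparametric perfusion CMR studies". CMR protocol and analysis says that CMR analysts are blinded to the invasive results.

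Other aims do use the invasive reference: concordance of MPR <2.0 with the endotypes, the MPR value with the highest AUC for microvascular angina, and accuracy for abnormal IMR, CFR and RRR. The box of secondary outcomes adds accuracy for endothelial dysfunction and has no change-in-diagnosis item.

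**The concern.** A proportion of changed diagnoses has no direction. A patient whose correct diagnosis becomes wrong adds as much to it as one whose wrong diagnosis becomes right. Of the substudy's listed aims, this is the only one that sets a CMR-based diagnosis beside what the cardiologist had concluded without it. A high figure could therefore be taken as support for usefulness when part of it is loss.

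The article itself gives a reason to expect some wrong changes: "Vasospastic angina may not be detected by conventional stress testing that routinely use adenosine", and adenosine is the stress agent in this study (Myocardial perfusion section). A normal scan could move a patient away from a correct vasospastic diagnosis, and the aim would count that as a change like any other.

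**Working it through.** The article gives no figure for this aim, so there is nothing to reproduce. Its sample sizes of 110 and 60 concern the correlation between CFR and MPR. The illustration below uses assumed values.

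**Inputs (assumed).** Score the diagnosis as microvascular angina yes/no. Let π be the prevalence by the invasive reference, s0 and c0 the sensitivity and specificity of the angiogram-based diagnosis, and s1 and c1 those of CMR. The two diagnoses are taken as independent given the reference.

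**Formulas.**

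- Right changes = π(1−s0)s1 + (1−π)(1−c0)c1
- Wrong changes = π·s0(1−s1) + (1−π)c0(1−c1)
- Proportion changed (the planned statistic) = right + wrong
- Net gain = right − wrong

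**Case A: π = 0.5, s0 = 0.30, c0 = 0.70** (a starting diagnosis no better than chance, since s0 + c0 = 1).

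- CMR at chance (0.5/0.5): right = 0.175 + 0.075 = 0.25; wrong = 0.075 + 0.175 = 0.25; changed 50%, net 0.
- CMR at 0.9/0.9: right = 0.315 + 0.135 = 0.45; wrong = 0.015 + 0.035 = 0.05; changed 50%, net +40 points.

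**Case B: π = 0.5, s0 = 0.50, c0 = 0.80** (a better starting diagnosis).

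- CMR at chance: right = 0.125 + 0.05 = 0.175; wrong = 0.125 + 0.20 = 0.325; changed 50%, net −15 points.
- CMR at 0.9/0.9: right = 0.225 + 0.09 = 0.315; wrong = 0.025 + 0.04 = 0.065; changed 38%, net +25 points.

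In case A the planned statistic does not distinguish the two tests. In case B it is higher for the worse one.

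**Range.** Over π from 0.3 to 0.7 and both starting diagnoses, a chance-level CMR always changes 50%, with net −21 to +8 points. A 90%/90% CMR changes 33% to 56%, with net +19 to +48 points. The ranges of the proportion changed overlap; those of the net gain do not.

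**Why the other aims do not supply the net gain.** For a yes/no diagnosis, net gain equals the accuracy of CMR minus the accuracy of the starting diagnosis. In case A this is 0.50 − 0.50 = 0 and 0.90 − 0.50 = +0.40. In case B the starting accuracy is 0.5×0.50 + 0.5×0.80 = 0.65, giving 0.50 − 0.65 = −0.15 and 0.90 − 0.65 = +0.25. The concordance and accuracy aims estimate the first term. No aim listed for the substudy estimates the second, or the paired difference.

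**Precision at the article's sample sizes (case A).** The paired standard error is √[(changed − net²)/n].

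- n = 110: chance CMR √(0.50/110) = 0.067, 95% CI half-width 13 points; 90%/90% CMR √(0.34/110) = 0.056, half-width 11 points.
- n = 60: √(0.50/60) = 0.091 and √(0.34/60) = 0.075, half-widths 18 and 15 points.

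Net gains of 0 and +40 points remain distinguishable at either size.

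**The case against.** The strongest reply is that a changed-diagnosis proportion is a legitimate descriptive measure of impact, and that the article never says a high value will be read as correctness. That is fair. A reader might infer that this aim is the main test of usefulness, but the article does not say so. The Aims are framed as diagnostic validity, and this aim is listed last. It is neither the primary outcome nor in the secondary outcomes box.

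A reader might also infer that CMR's correctness goes untested. It does not: a worthless test would show up in the concordance, AUC and accuracy analyses. What is missing is narrower, namely the gain or loss relative to the cardiologist's diagnosis.

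A third tempting reading uses the 73% sensitivity and 74% specificity in the Literature review and supposes that everyone starts as non-cardiac. At 50% prevalence, 0.5×0.73 + 0.5×0.26 = 49.5% of diagnoses change, close to the 50% of a coin toss. That comparison should not be used:

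- It depends on the prevalence: the figure is 40.1% at 30% and 58.9% at 70%.
- With a uniform start, every change is a CMR positive, so the net gain would already follow from the planned concordance analysis.
- The article gives no support for a uniform starting diagnosis.
- The accuracies belong to a semiquantitative index in a cohort of women, not to quantitative MPR <2.0.

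Two practical objections stand in part. The SAP is not shown and may score the changes, but the article names a comparator and it is not the reference. The article also gives no rule that turns CMR results into one of five endotypes, and a full three-way table in 60 to 110 patients would be sparse. The aim as written needs a CMR-based diagnosis in any case, so this argues for simpler scoring and does not remove the problem. Finally, invasive testing is planned in both arms, but that does not guarantee an endotype for every patient: the sample size section allows for only 60 with available data.

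**Conclusion.** The point holds for this aim. As worded, the proportion changed cannot separate improvement from harm, and on its own it cannot support the usefulness hypothesis. The same 50% can go with a net gain of 0 or of +40 points. These sizes rest on assumed prevalence, assumed accuracy of the starting diagnosis and conditional independence. They show what the statistic cannot distinguish and do not predict the study's result. The logical point needs none of these assumptions.

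The consequence is limited to the interpretation of one aim. The primary outcome, the sample size and the reference-based accuracy analyses are not affected.

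**What to change.** Keep the proportion changed. Among patients with an available invasive endotype, also report the proportion changed to agree with the reference minus the proportion changed away from it, with a paired 95% CI, and state how many patients had no endotype. Make microvascular angina yes/no the main scoring. This is the classification MPR can address, and it avoids changes from one wrong endotype to another, which are neither gain nor loss. Describe changes in patients with vasospastic or mixed endotypes separately, because the article expects adenosine stress to miss some vasospasm.

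The cost is a sentence in the aims or SAP and one extra table. It uses the planned invasive results, the recorded starting diagnosis and the CMR-based diagnosis that the aim already requires. The downsides are sparse cells in the vasospastic and mixed rows and a headline figure likely to look somewhat less favourable than the raw proportion.

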## Methods and analysis

### Study design

Prespecified substudy of the CorMicA stratified medical therapy clinical trial.

### Setting

Patients referred from 14 acute hospitals to two large regional UK hospitals (Golden Jubilee National Hospital and Hairmyres Hospital) providing invasive care to all patients in the West of Scotland (population 2.5 million). All CMR studies will be performed at the Golden Jubilee National Hospital.

### Participants

Consecutive outpatients undergoing clinically indicated elective diagnostic angiography for investigation of suspected angina will be screened and invited to participate in the CorMicA trial. Informed consent is obtained before the invasive coronary angiogram. A minimum of 400 consecutive patients undergoing elective invasive coronary angiography is expected to be screened to enrol 150 subjects with ANOCA within 24 months. Consenting patients who are not randomised (e.g. demonstrated to have obstructive epicardial disease or logistical reasons) will enter a registry. Only patients randomised in the CorMicA trial (both in the intervention and control groups) are eligible to participate in the CorCMR substudy.

#### Inclusion criteria

Age ≥18 years, a clinically indicated plan for invasive coronary angiography and symptoms of angina (according to the Rose angina questionnaire).

#### Exclusion criteria

A non-coronary indication for invasive angiography (e.g. valvular heart disease and cardiomyopathy), obstructive epicardial CAD disease evident in a main coronary artery (diameter >2.5 mm) (defined as diameter stenosis >50% or FFR ≤0.80) and contraindication to contrast-enhanced CMR (glomerular filtration rate <30 mL/min, CMR unsafe devices).

### CMR protocol and analysis

Patients will undergo perfusion CMR within 42 days of the CorMicA trial invasive coronary artery function testing. CMR studies will be performed at 1.5 Tesla (Siemens MAGNETOM Avanto, Erlangen, Germany), and patients will undergo a standardised CMR protocol. All patients will be asked to abstain from caffeine-containing beverages or foodstuffs for 24 hours and vasoactive medications for 48 hours prior to the CMR examination. All scan acquisitions will be spatially coregistered. All CMR analyses will be performed by analysts blinded to the invasive coronary artery function test results. The standardised CMR protocol is demonstrated in figure 2.

**Figure 2 F2:**
[figure not shown]
CorCMR multiparametric imaging protocol. CorCMR, Coronary Microvascular Angina Cardiac MRI.

#### Myocardial perfusion

Stress and rest first-pass perfusion imaging will be performed using an echo planar imaging dual-sequence investigational perfusion method, which consists of a low resolution arterial input function image, followed by three short axis (base, mid and apex) myocardial images during each R–R interval.^40–42^ Vasodilator stress will be achieved with adenosine infusion 140–210 µg/kg/min for 3 min. Resting first-pass perfusion will be performed at least 10 min later.

The raw stress and rest perfusion images will be qualitatively assessed for inducible or fixed perfusion defects. Perfusion defects will be reported on a segmental basis according to the American Heart Association 16-segment model.^43^ Dark banding artefact will be adjudicated based on standardised criteria.^22^

Pixel-wise perfusion maps will be generated and analysed to derive fully quantitative MBF estimates on a pixel-wise basis in mL/g/min of myocardium. The pixel-wise perfusion method uses a series of automated postprocessing steps on the raw Digital Imaging and Communications in Medicine images to generate fully quantitative pixel maps.^21^ The pixel-wise time-signal intensity curves will then be quantified using model-constrained Fermi deconvolution.^44–46^

The myocardial perfusion dyssynchrony index is a novel perfusion metric that assesses temporal differences in the distribution of gadolinium-based contrast media myocardial wash-in. This index has the potential to increase the diagnostic sensitivity and specificity of perfusion CMR for abnormalities of myocardial perfusion in patients with ANOCA.^39^ Global perfusion dyssynchrony indices will be measured as both variance [s^2^] and percentage coefficient of variation of time to maximum signal intensity upslope and time to peak myocardial signal intensity enhancement.

#### Extracardiac anatomy and LV volumes, function and mass

Fast gradient echo images in the axial, coronal and sagittal planes will be qualitatively assessed for extra cardiac anatomy and pathology and clinically relevant incidental findings.

Steady-state free procession ‘cine’ imaging using a trueFISP sequence (multislice single-shot breath-hold true fast imaging) will be performed in the three long-axis and short-axis planes for assessment of LV volumes, function and mass.

#### Myocardial tissue characterisation

Native T1 mapping will be performed using a modified look-locker inversion recovery investigational prototype sequence. Images will be obtained in three short-axis images (base, mid and apex). T1 mapping will be performed pre- and post-gadolinium contrast to assess the myocardial native T1 relaxation time and estimate the myocardial extracellular volume (ECV) in both the mid-septum and globally.^47^ For the calculation of ECV, blood haematocrit will be measured at baseline on enrolment into the CorMicA trial. ECV mapping analysis will be performed offline using proprietary software.

LGE imaging will be performed using a segmented phase-sensitive inversion recovery turbo fast low-angle shot imaging sequence.^48^ Images will be obtained in the three long-axis planes and short-axis images covering the entire LV myocardium. The pattern and burden of hyperenhancement will be qualitatively and quantitatively assessed.

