### Primary and secondary outcomes

#### Primary outcome

Abnormal myocardial perfusion reserve (global MPR <2.0).

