#### Secondary outcomes

A summary of the secondary outcomes is shown in Box 1.

Box 2.CorCMR substudy secondary outcomes and analysesLV volumes, function and massLV EFLVEDVLV EDV indexLV ESVLV ESV indexLV massLV mass indexLV COLV CO indexAtrial areaLeft atrial area (cm^2^)Left atria dilated (Y/N)Right atrial area (cm^2^)Right atria dilated (Y/N)Qualitative perfusion analysisAbnormal perfusion (Y/N)Number of abnormal segments (n)Transmurality of perfusion defects (%)Pattern (epicardial, microvascular, mixed and equivocal)Quantitative perfusion analysisGlobal MPR <2.0 (Y/N)Segmental/AHA MPRGlobal stress and rest MBFSegmental/AHA territory stress and rest MBFGlobal stress endocardial:epicardial MPR ratioSegmental/AHA territory endocardial:epicardial MPR ratioPerfusion dyssynchrony analysisMyocardial perfusion dyssynchrony index (variance and coefficient of variation of the time to maximum signal intensity upslope and time to peak myocardial signal intensity enhancement)Adenosine vasodilator stress responseSplenic switch-off (Y/N)HR and BPchangeRate-pressure product at rest and stressLate gadolinium enhancement imagingAbnormal LGE (Y/N).Number of affected AHA segments (n)Pattern of abnormal LGE (ischaemic and non-ischaemic)Myocardial infarct scar burden (transmurality, infarct mass, infarct mass as percentage LV mass)Native T1 and ECV mappingNative T1 (global and midseptal values)ECV (global and midseptal values)Myocardial strainFeature-tracking and DENSE (two methods)Longitudinal strain (global and by AHA segment)Circumferential strain (global and by AHA segment)Radial strain (global and by AHA segment)Incidental findingsPresent (Y/N)Clinically significant (Y/N)Associations of abnormal perfusion with baseline characteristicsSex, age and traditional CAD risk factorsCAD risk scores (JBS3 and ASSIGN)Gensini score of epicardial plaque burdenAssociations of abnormal perfusion with invasive coronary artery function testing dataAssociation of myocardial perfusion with IMR, CFR, RRR and endothelial function testing (continuous and binary)Subset of patients with multivessel invasive coronary artery function measurementsAssociation with clinical diagnosis (ANOCA disease endotype)Associations of abnormal perfusion with baseline CMR dataLV volumes and massMyocardial strainNative T1 relaxation time and ECVPresence of LGEDiagnostic accuracyDiagnostic accuracy of quantitative perfusion CMR to detect abnormal IMR, CFR, RRR and endothelial dysfunctionAHA, American Heart Association; ANOCA, angina with no obstructive coronary artery disease; BP, blood pressure; CFR, coronary flow reserve; CAD, coronary artery disease; CO, cardiac output; CorCMR, Coronary Microvascular Angina Cardiac MRI; EF, ejection fraction; EDV, end-diastolic volume; ESV, end-systolic volume; ECV, extracellular volume; HR, heart rate; IMR, index of microcirculatory resistance; LV, left ventricular; LGE, late gadolinium enhancement; MBF, myocardial blood flow; MPR, myocardial perfusion reserve; RRR, relative resistance ratio,

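### ECV is calculated from a haematocrit taken at trial enrolment, up to 42 days or possibly more before the scan, so it carries avoidable error wherever haematocrit has changed

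*Protocol article*

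**What the plan says.** Under Myocardial tissue characterisation, T1 maps are acquired before and after gadolinium at the CMR visit and ECV is estimated from them. The blood value that completes the calculation is tied to a different occasion: "For the calculation of ECV, blood haematocrit will be measured at baseline on enrolment into the CorMicA trial". No repeat sample at the CMR visit is mentioned.

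The section CMR protocol and analysis sets the interval to the scan: "Patients will undergo perfusion CMR within 42 days of the CorMicA trial invasive coronary artery function testing". This is an upper limit; no minimum or typical interval is given.

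When enrolment falls is less clear. Under Participants, "Informed consent is obtained before the invasive coronary angiogram". The same section also speaks of the number of patients who "is expected to be screened to enrol 150 subjects with ANOCA within 24 months", and ANOCA is a status known only once the angiogram has been done. The description of the parent trial adds: "Eligible patients with ANOCA (n=150) will be immediately randomised 1:1".

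ECV is a secondary outcome, listed as "ECV (global and midseptal values"), and it appears again in that list among the CMR measures to be related to abnormal perfusion. The related aim begins "The proportion of patients with ANOCA and abnormal myocardial tissue characterisation derived from CMR" and names T1 mapping and late gadolinium enhancement (LGE). The primary outcome is "Abnormal myocardial perfusion reserve (global MPR <2.0").

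**The concern.** ECV is the myocardial partition coefficient multiplied by one minus the haematocrit. The coefficient comes from the T1 values of the blood and myocardium imaged on the scan day, so the haematocrit should describe that same blood. The article combines it with a value from another day and treats patients scanned soon after sampling and patients scanned six weeks later as equally well described by it.

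What is at stake is the precision of one secondary outcome and of its planned associations. Drift that varies between patients adds noise to ECV and pulls any correlation with perfusion towards zero. The article's Literature review calls the role of ECV in these patients uncertain and cites a study of 54 women that found no correlation with coronary vascular function. Avoidable attenuation would make a further null result harder to interpret. The scan-day value cannot be recovered afterwards if no sample was taken.

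**Working it through.** The article states no haematocrit variability, ECV value or ECV error, so there is no figure of its own to reproduce. The check has two parts.

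**1. The lag between sample and scan**

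- Invasive test to CMR: 0 to 42 days (CMR protocol and analysis).
- If enrolment means randomisation at the angiogram, the lag from sample to scan is 0 to 42 days.
- If enrolment means consent before the angiogram, the lag is 0 to 42 days plus the time from consent to angiogram, which is not stated.

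A lag of up to 42 days is therefore allowed on either reading. A longer one is possible but not shown.

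**2. The size of the error**

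All inputs here are assumptions, not figures from the article: haematocrit (Hct) 0.42, ECV 26%, between-patient ECV SD 3 points, haematocrit change d of 0.01, 0.02 or 0.03.

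The relation is ECV = λ × (1 − Hct), where λ is the partition coefficient. A change d gives an absolute ECV error of λ × d = ECV × d/(1 − Hct) and a relative error of d/(1 − Hct).

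- d = 0.01: 26 × 0.01/0.58 = 0.45 points (1.7% relative)
- d = 0.02: 26 × 0.02/0.58 = 0.90 points (3.4% relative)
- d = 0.03: 26 × 0.03/0.58 = 1.34 points (5.2% relative)

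If haematocrit falls after the sample, the older and higher value makes (1 − Hct) too small and ECV too low. If it rises, ECV is too high.

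Now let d instead be random between patients, with an SD of 0.01, 0.02 or 0.03. The error SD in ECV is then 0.45, 0.90 or 1.34 points. Reliability = 3²/(3² + error SD²), and the observed correlation is the true one times √reliability:

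- SD 0.01: 9/(9 + 0.20) = 0.98, so 0.30 × √0.98 = 0.297
- SD 0.02: 9/(9 + 0.80) = 0.92, so 0.30 × √0.92 = 0.287
- SD 0.03: 9/(9 + 1.81) = 0.83, so 0.30 × √0.83 = 0.274

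**Sensitivity to the assumptions.** With haematocrit 0.36 to 0.45 and ECV 25% to 28%, the absolute error is about 0.4 to 0.5 points at d = 0.01, 0.8 to 1.0 at 0.02 and 1.2 to 1.5 at 0.03. With ECV 27%, haematocrit 0.42, ECV SD 2.5 to 3.5 points and drift SD 0.01 to 0.03, a correlation is multiplied by 0.87 to 0.99, so 0.30 becomes 0.26 to 0.30. At d = 0 the error is zero.

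The true correlation of 0.30 is illustrative. The Sample size calculation uses 0.3 for invasive CFR against MPR, not for ECV, and no sample size or power figure in the article depends on ECV.

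**The case against.** The strongest case against the point is that it is small and rests on assumed drift. That stands in part. Forty-two days is a maximum, the article does not say how much haematocrit varies in these outpatients, and at a drift SD of 1 point the loss of correlation is about 1%.

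A reader might infer more than the text supports, in four ways:

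- *That every ECV value is wrong.* Error arises only where haematocrit has changed between sample and scan. Some scans may follow soon after the sample, and in some patients the value will be stable.
- *That the sample precedes the angiogram and the lag exceeds six weeks.* It is consent that is stated to come first, not blood sampling. Enrolment is also used of patients already shown to have ANOCA.
- *That fluid or blood loss at catheterisation biases all ECV values low.* The article says nothing about either, nor that any such effect would persist to the scan. A uniform shift would in any case mainly rescale ECV and leave its correlation with MPR essentially unchanged; it is variation between patients that attenuates.
- *That the tissue-characterisation aim or the primary outcome is compromised.* Native T1, LGE and global MPR, as described, do not use haematocrit.

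None of this removes the core. The timing is a stated rule, not a detail left to a longer document, and it ties a scan-day calculation to blood from another day.

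**Conclusion.** The point holds as a modest measurement weakness in one secondary outcome and its associations. It is not an internal contradiction and does not threaten the main result. The timing rule and the 42-day allowance are in the text; the size is not. Within the assumed range of 1 to 3 haematocrit points, the ECV error runs from under half a point to about 1.3 points, and attenuation of a correlation of 0.30 runs from negligible to about 0.27. A scan-day sample would remove this drift component entirely; assay error and T1 measurement error would remain.

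**What to change.** Amend the sentence under Myocardial tissue characterisation so that haematocrit is measured on the day of the CMR and that value is used for ECV. The enrolment value would serve only when the scan-day sample is missing, and ECV values obtained that way would be flagged in the dataset.

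The article does not describe a cannula, but the adenosine infusion and gadolinium contrast already call for venous access at the scan, so no extra visit or separate procedure should be needed. The cost is one small blood tube and one assay per CMR visit, and possibly a minor update to the ethics approval and consent. No sample size or power figure changes.
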